### Study procedures

2.4

An overview of the respective assessments and intervention dates can be found in Table 1. Children and students are assessed three times, parents three to six times, and teachers once. The surveys for parents, children, teachers, and students each take approximately 20–30 min. The survey for the children takes place onsite at their school and is supervised by trained staff members. The children complete the questionnaires using tablets provided by the school (online version). If tablets are not available at the school, paper-and-pencil questionnaires are used instead. Surveys for parents, students, and teachers are available online, with the participants receiving a link to the online questionnaires via email.

**Table 1 tab1:** Schedule of enrollment, interventions, and assessments.

Timepoint	Enrollment	Post-allocation					
	−t_1_	t_1_	t_2_	t_3_	t_4_	t_5_	t_6_
Eligibility screen, informed consent and allocation	X				X		
Interventions							
Talking mental health (IG)		X					
Talking mental health (CG)				X			
Emotion focused skills training					—		
Assessments							
*Parents*: stigma (PMHSS), help-seeking (GHSQ & AHSQ), mental health parents (PHQ-4), mental health children (KIDSCREEN-10), mentalizing (PRFQ)^1^, parental self-efficacy (FSW)^1^		X	X	X	X	X	X
*Children*: stigma (PMHSS), mental health literacy (vignettes), mental health (KIDSCREEN-10), help-seeking (GHSQ & AHSQ), satisfaction		X	X	X			
*College Students*: stigma (PMHSS & OMS-HC), satisfaction		X	X	X			
*Teachers*: stigma (PMHSS), satisfaction				X			

IG, Intervention group; CG, Control group; PMHSS, Peer Mental Health Stigmatization Scale; PHQ-4, Patient Health Questionnaire; KIDSCREEN-10; GHSQ, General Help-Seeking Questionnaire; AHSQ, Actual Help-Seeking Questionnaire; OMS-HC, Opening Minds Stigma Scale for Health Care Providers; PRFQ, Parental Reflective Functioning Questionnaire; FSW, Parenting self-efficacy questionnaire.

1 Only at t_4_, t_5_, and t_6_.

To implement the project in elementary schools in Heidelberg, approval was obtained from the relevant school authorities. In addition, school administrations must agree that the prevention program and surveys can be carried out. Project staff also attend parent-teacher conferences and student body meetings to provide parents, teachers and college students with detailed information about the program. The project staff presents the project and the data collection process. Approximately 1 week later, signed consent forms are collected from the schools and students. After the parents’ school evening, all parents receive the link to the first survey (t_1_). The children in the intervention group are assessed for the first time immediately prior to the intervention (t_1_), then at least 1 week later (t_2_) and again 6 weeks later (t_3_). For children in the control group, the first assessment is scheduled after the parent-teacher conference (t_1_), 1 week later (t_2_), and at least 6 weeks later (t_3_). In the control group, the final assessment takes place just before the TMH prevention program. At the same time as the child assessments, parent assessments 2 and 3 are sent by email. Following the prevention program, teachers also receive an invitation to participate in their survey.

After the third survey, parents can request feedback based on their assessment of whether their child’s mental health is below average, average or above average compared with other children of the same age. Parents can also provide their email address if they like a psychological consultation. The consultation is conducted by a psychologist (SP) and lasts 50 min. During the consultation, the current problem situation is recorded, information about appropriate help is given, and the parent training is introduced and offered. The parent training takes place afterwards. Parents are assessed again before the parent training (t_4_), after the parent training (t_5_), and again 4 months later (t_6_). To take part in t_4_ to t_6_, parents must give their informed consent online. For this part of the study, parents who indicated in the first consent form that they would like to be contacted again are contacted. Parents who take part in the parent training and those who do not, can take part in these three additional surveys.

Finally, college students who participate in Vitaphilie are recruited at the beginning of each semester. At this point in time, both the intervention group and the control group receive the first survey. In the middle of the semester, the control group completes the second questionnaire, whereas each person in the Vitaphilie group receives an email with the post-intervention survey after completing the prevention program. Both groups of students complete the follow-up questionnaire at the end of the semester.

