This research project investigates whether the school-based prevention program “Talking mental health” (TMH) can increase mental health literacy and help-seeking behavior while reducing the stigma of mental disorders. The primary aim of the prevention project is to improve children’s knowledge and attitudes toward managing difficult emotions. Parents are supported to talk to their children about their feelings and, if necessary, to access appropriate support services. In addition, the effects on college students implementing and being trained in the program are examined.

We expect that children who have completed the TMH program (compared to those in the waitlist control group) will show improved knowledge and skills in managing mental health problems and difficult emotions (increased mental health literacy; Hypothesis 1a), greater willingness to talk about their difficult feelings (increased intentional help-seeking behavior, Hypothesis 1b), increased actual help-seeking behavior (Hypothesis 1c), and reduced stigmatization of mental health problems (Hypothesis 1d). We expect these effects to be present both 1 week after the intervention and at least 6 weeks later. We expect that in the intervention group, an increase in mental health literacy will lead to a decrease in stigma, which in turn will cause an increase in help-seeking behavior (Hypothesis 1e).

Additionally, we expect that parents of children who completed the prevention program (compared with parents in the waitlist control group) will show increased help-seeking behavior for their children (Hypothesis 2a) and reduced stigmatization of mental health problems (Hypothesis 2b).

College students trained in and implementing the TMH program should show less stigmatization toward others than should college students in the control group (Hypothesis 3).

Finally, we expect parents who participate in the parent training program (Emotion focused skills training; EFST-P) and their children to demonstrate improved mental health after the conclusion of the program (Hypothesis 4a). This effect is achieved by increasing parents’ self-efficacy (Hypothesis 4b) and mentalization skills (Hypothesis 4c).

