### Design and randomization

2.1

This study evaluates the “Talking mental health” prevention program using cluster randomization with a pre-post follow-up measurement approach. Elementary schools are randomly assigned to either the experimental condition or the waitlist control group by the study coordinator (SP) using digital coin toss^1^. The assignment is documented in an electronic file. Neither stratification nor block randomization are applied. The participants in the experimental condition are instructed to complete a questionnaire just before the prevention program. The post-measurement takes place at least 1 week after the intervention, and the follow-up at least 6 weeks later. In comparison, all three measurements in the waitlist control group are taken at the same time intervals, but the intervention takes place only after the last measurement.

A quasi-experimental design is used for the group of college students who carry out the prevention program. We compare students from the student organization “Vitaphilie” (Medical Students’ Association of the Heidelberg University), who are trained to deliver the program, with students from other medical student organizations not trained in the program. The students assign themselves to the student organizations independently (quasi-experimental; students carrying out the training vs. students from other student organizations).

Upon request and if needed, a psychological counseling session for the parents and subsequent parent training are offered after completion of the project (parent skills training based on EFST-P; Dolhanty et al., 2022). Parents are surveyed before and after the training, and 4 months later, and compared with parents who did not receive the training (quasi-experimental allocation).

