#### Talking mental health

2.5.1

“Talking mental health” is a school-based prevention program addressing 3rd and 4th graders. The aim of the intervention is to raise awareness of mental health by covering different types of feelings, teaching children how to talk about and manage their feelings, when to seek help and how to support others.

TMH uses child-friendly material to cover the following topics: (a) what is mental health, (b) what are “small” (everyday feelings) and “big” (feelings that last long and impact daily life and mental health) feelings, (c) how can I deal with these feelings, (d) how can I talk about difficult feelings, (e) where can I get help, and (f) how can I be a good listener when someone approaches me? The program is delivered in a one-day workshop during school hours in the classroom (4 school hours) by 4 to 5 medical or psychology students (facilitators). The class teacher is present to support the facilitators.

The content is introduced to the children through a short video (5 min, English version^2^ and German version^3^). The video tells the story of 10-year-old Luca, who faces emotional challenges, by describing their feelings and offering possible coping strategies, as well as showing how seeking help can contribute to mental health. During the session, small parts of the video are shown and discussed with the children. To create a safe and private environment, each facilitator works with 5–6 children at an individual table. Each table group has a “mood barometer,” which is used to check the children’s emotional state. Each child is also given a handout called “My Mental Health License” to take home. Throughout the session, each aspect is marked down in there. The program also includes a section where possible points of contact, both informal and formal, are worked out with the children. In addition to the video, other materials are used to work on the themes mentioned above. For example, the distinction between “small” and “big” feelings can be explored by sorting statements and brainstorming personal experiences. The children also create their own support circle. They practice raising difficult topics by taking turns using conversation starters with their peers. Role play is also used to practice validating the feelings of others through attentive listening. Parents are provided with online information material to guide them on the following topics:

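### Control parents' last online survey is emailed just before their child's class receives the programme, so answers given later may follow exposure and dilute the t3 parent contrast

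*Protocol article*

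**What the plan says.** Section 2.1 of the protocol article sets the rule for the waitlist arm: "all three measurements in the waitlist control group are taken at the same time intervals, but the intervention takes place only after the last measurement".

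Section 2.4 gives the procedure. For the control arm, "In the control group, the final assessment takes place just before the TMH prevention program". For parents, "At the same time as the child assessments, parent assessments 2 and 3 are sent by email". Table 1 agrees: the control group's programme and the parents' t3 survey share the t3 column.

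The mode of survey differs between children and parents. For children, "The survey for the children takes place onsite at their school and is supervised by trained staff members". For adults, "Surveys for parents, students, and teachers are available online, with the participants receiving a link to the online questionnaires via email".

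Section 2.5.1 describes a one-day workshop of 4 school hours and two ways in which it can reach parents. One is through the child: "Each child is also given a handout called “My Mental Health License” to take home". The other is direct: "Parents are provided with online information material to guide them on the following topics". The topics are how to talk with the child about feelings and where to find professional support. The article does not say when control parents receive this material.

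The parent hypotheses in the Introduction are that parents in the intervention arm, compared with waitlist parents, "will show increased help-seeking behavior for their children (Hypothesis 2a) and reduced stigmatization of mental health problems (Hypothesis 2b").

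**The concern.** The waitlist comparison at t3 needs control answers that precede the programme. A child's supervised questionnaire can be completed before the workshop starts. A parent's survey is only dispatched at that moment. Because the workshop takes a single school day, a parent who opens the link a little later may already have a child who has attended and brought the handout home.

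The content is close to what the parent scales measure. The children work on naming feelings, starting conversations and finding help, and the parent material covers the same ground. Stigma (PMHSS) and intended help-seeking (GHSQ) could respond quickly. Under the intention-to-treat analysis in section 2.8, a late control answer counts as unexposed. If the programme works, this makes it look less effective in parents at t3. Once the control classes have been treated, no later randomised contrast can replace t3.

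**Working it through.** **Order of events in a control class, from sections 2.1, 2.4 and 2.5.1**

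1. The children's t3 takes place on site, just before the programme. Their last measurement precedes treatment, as section 2.1 requires.
2. The parents' t3 link is emailed at the same time as the children's t3.
3. The programme is delivered within one school day.
4. The parent completes a 20–30 minute online survey, unsupervised, at a time of their choosing.

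Nothing in the stated sequence puts step 4 before step 3. The rule holds for children by procedure. For parents it holds only if they answer promptly.

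**The t2 contrast.** The Discussion gives minimum intervals of 1 week from survey 1 to survey 2 and 6 weeks from survey 1 to survey 3. On those minima the control parents' t2 link goes out 6 − 1 = 5 weeks before t3, so ordinary delay does not carry it past the programme.

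**Which outcomes are affected.** PMHSS asks about current attitudes and GHSQ about intentions. AHSQ asks about help sought in the past 6 months, so a few days of exposure can change it very little.

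**Size, as a worst case.** Let f be the share of control t3 parent answers given after exposure, and suppose that each carries the full programme effect at once. Then:

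- observed contrast = d × (1 − f)
- sample multiplier to keep the same power = 1 / (1 − f)²

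The plan's own figure reproduces: 35 classes × 15 = 525, or 262.5 per arm. Section 2.3 names a moderate effect without a number and gives no intraclass correlation (ICC). Assumed here: d = 0.5, with 0.3 as a lower value; ICC 0.05; two-sided alpha 0.05; SD 1.

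- Design effect = 1 + 14 × 0.05 = 1.70
- Effective n per arm = 262.5 / 1.70 = 154.4
- Power ≈ Φ(d(1 − f) × √(154.4 / 2) − 1.96)

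| f (assumed) | contrast retained | d = 0.5 becomes | sample multiplier | power, d = 0.5 | power, d = 0.3 |
|---|---|---|---|---|---|
| 0 | 1.00 | 0.50 | 1.00 | 0.99 | 0.75 |
| 0.10 | 0.90 | 0.45 | 1.23 | 0.98 | 0.66 |
| 0.25 | 0.75 | 0.375 | 1.78 | 0.91 | 0.51 |
| 0.50 | 0.50 | 0.25 | 4.00 | 0.59 | 0.26 |
| 0.75 | 0.25 | 0.125 | 16.00 | 0.19 | 0.10 |

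The power columns are illustrations only. They assume that all 525 parents answer and that classes are the clusters, whereas section 2.1 randomises schools, so real power may be lower throughout. The retained share and the multiplier do not depend on those two assumptions.

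**The case against.** The strongest reply is that section 2.1 already states the right rule, and that a response window or link closure is detail which an article may leave to the full protocol. That is fair, and a missing deadline is not the point here. The point is the stated timing: sending the survey at the same moment as an assessment held just before the programme leaves little room for any window. How little is unknown, since the article does not say how long that gap is.

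Several stronger readings are tempting, and the documents do not support them:

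- *Many control parents answer late.* No response times are given. Every f above is an assumption, and full immediate effect is the extreme case.
- *Control parents receive the parent material on the programme day.* No release date is stated for that arm. If the material is held back until t3 closes, only exposure through the child remains.
- *Both parent hypotheses are lost.* The t2 contrast is clean and AHSQ is hardly touched. H2a and H2b also name no time point; the expectation of effects at 1 and 6 weeks is written for the child hypotheses.
- *Intervention parents run the same risk at baseline.* The t1 link goes out after the parents' school evening and is not tied to the programme day. Late completion is possible but less likely.

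It also stands that the bias runs towards no difference, so it would not create a false claim of benefit. Deleting late control answers from the main analysis would be open to challenge: it removes slow responders from one arm only, under a declared intention-to-treat analysis, and slow responders may differ in engagement or stigma.

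**Conclusion.** The point holds in a limited form. The stated procedure secures the waitlist rule for children and not for parents. Control t3 parent answers given after the programme day may be exposed. If the programme works, they bias the t3 contrast towards no difference, chiefly for PMHSS (H2b) and GHSQ intentions (H2a). AHSQ is little affected, and the t2 parent contrast is not affected.

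The size cannot be read from the article. With a share f fully and immediately affected, the contrast keeps 1 − f of its true value; partial effects give less dilution. At d = 0.5 and the assumed ICC of 0.05, a share of 0.25 lowers power only from 0.99 to 0.91. At d = 0.3 the same share lowers it from 0.75 to 0.51. Whether this matters in practice depends on the submission dates, which should be examined before the parent results are analysed.

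**What to change.** **Before analysis.** Compare each parent's t3 submission date with the programme date of the child's class, assuming that the online tool stores it. Report how many control answers came after the programme, and decide in advance how answers given on the programme day itself are classed. Keep the intention-to-treat analysis of all answers as the main one. Prespecify a sensitivity analysis for H2a and H2b that treats post-programme control answers as missing under the planned multiple imputation, and present the t2 contrast beside it as the uncontaminated comparison. Check t1 submission dates in the intervention arm in the same way.

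**For control classes still to run.** Close the parents' t3 survey before the programme day and release the parent material only after it has closed, keeping the interval of at least 6 weeks. The trial status section reports data from 30 classes and 6 more planned, so this reaches at most the control classes among those 6. The analysis rule therefore matters more.

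**Cost.** A date check, one extra analysis and a short scheduling gap before the programme. The sensitivity analysis loses some parent data and may favour prompt responders, which is why it should accompany the main analysis and not replace it.

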### Intervention

2.5

#### Talking mental health

2.5.1

“Talking mental health” is a school-based prevention program addressing 3rd and 4th graders. The aim of the intervention is to raise awareness of mental health by covering different types of feelings, teaching children how to talk about and manage their feelings, when to seek help and how to support others.

TMH uses child-friendly material to cover the following topics: (a) what is mental health, (b) what are “small” (everyday feelings) and “big” (feelings that last long and impact daily life and mental health) feelings, (c) how can I deal with these feelings, (d) how can I talk about difficult feelings, (e) where can I get help, and (f) how can I be a good listener when someone approaches me? The program is delivered in a one-day workshop during school hours in the classroom (4 school hours) by 4 to 5 medical or psychology students (facilitators). The class teacher is present to support the facilitators.

The content is introduced to the children through a short video (5 min, English version^2^ and German version^3^). The video tells the story of 10-year-old Luca, who faces emotional challenges, by describing their feelings and offering possible coping strategies, as well as showing how seeking help can contribute to mental health. During the session, small parts of the video are shown and discussed with the children. To create a safe and private environment, each facilitator works with 5–6 children at an individual table. Each table group has a “mood barometer,” which is used to check the children’s emotional state. Each child is also given a handout called “My Mental Health License” to take home. Throughout the session, each aspect is marked down in there. The program also includes a section where possible points of contact, both informal and formal, are worked out with the children. In addition to the video, other materials are used to work on the themes mentioned above. For example, the distinction between “small” and “big” feelings can be explored by sorting statements and brainstorming personal experiences. The children also create their own support circle. They practice raising difficult topics by taking turns using conversation starters with their peers. Role play is also used to practice validating the feelings of others through attentive listening. Parents are provided with online information material to guide them on the following topics:

(1) How do I talk to my child about difficult feelings and mental health?(2) Where can I go for professional support for my child in and around Heidelberg?

The material on “How do I talk to my child about difficult feelings and mental health?” were developed using recommendations for communicating with children (Döpfner, 2019) and existing material from the Anna Freud National Center for Children and Families (2025), e.g., how to start a conversation with children about feelings and general recommendations (curiosity, staying calm, open questions, taking children seriously, praise). The material on “Where can I go for professional support for my child in and around Heidelberg?” were developed by looking at existing help centers in Heidelberg, Germany. Parents were given information on which (professional) contact point is suitable for which difficulties, e.g., the difference between a psychiatrist and a psychotherapist.

TMH was originally developed by the Anna Freud National Center for Children and Families (Sharples et al., 2017). In 2019, our research team translated and adapted the intervention for Germany through a pilot study. In contrast to the original program, our program is not carried out by the teacher but by college students. A systematic review found that teachers frequently report stress when simultaneously acting as educator and program facilitator (Schäfer et al., 2025). In addition, a lack of time represents a common barrier keeping teachers from implementing prevention programs (Schäfer et al., 2025). Fortunately, students from the “Vitaphilie” working group were available and interested in cooperating with us. This allowed us to assign several facilitators to a class, with each student serving as the contact person for a group of five to seven children. Previous research has examined the involvement of peer facilitators in health education and has shown that this approach can help fill gaps on an equal footing that professionals are sometimes unable to reach (Dodd et al., 2022). This approach was also favored by the schools we recruited so far. Our adaptation lasts 4 school hours (3–3.5 h), whereas the original program takes 1–1.5 h. It has been suggested that interactive methods facilitate learning in mental health prevention programs (Schäfer et al., 2025). Therefore, we decided to explore the different topics in greater depth, with the use of more didactic methods and materials (e.g., the mood barometer, the role play). To include this, we had to extend the program while also making sure it will not be perceived as too lengthy (Schäfer et al., 2025). In line with the recommendations of Ma et al. (2023b), our program provides more detail about possible support services, such as doctors, psychologists, and therapists, and promotes the German helpline for children (“Nummer gegen Kummer”). The original prevention program did not include practical, targeted help-seeking content. Another extension is the introduction of a “toolbox” in which children can collect skills for dealing with small feelings. Other research projects have also recommended the inclusion of specific strategies for dealing with emotions (Kuyken et al., 2022). As additional interactive content, we have included an activity in which the whole class physically acts out different feelings, e.g., disgust, anger, and happiness.

